### Program

Moving Stories is a game-based school program, which consists of three parts: (1) an introduction lesson; (2) a single-player, mobile, 3D video game; and (3) a contact session with someone with lived experience with a depressive disorder. The program targets three components of mental health literacy, specifically regarding depression, namely (1) recognition of when a disorder is developing, (2) knowledge of help-seeking options and treatments available, and (3) first aid skills to support others who are developing a mental disorder or are in a mental health crisis [10]. Moreover, the program aims to decrease stigma around depression among youth. Moving Stories has been developed for high school students and should be offered to an entire class. The program is delivered within one week, making it convenient to incorporate into schools.

During the introductory lesson, adolescents who were in a class together were asked to download the game on their mobile phone. Moving Stories can be downloaded from the Google Play Store or Apple’s App Store (iOS). All adolescents in the class received a classroom password to be able to play the game. This password was linked to their class schedule, allowing for joint playing time and feedback moments. The adolescents were then able to watch an introductory video about the game. The video game is about a character, Lisa, who is the player’s fictional cousin (see Figure 2). The introductory video talks about who she is and what the relationship is between her and the player. The video also conveys that Lisa has not been feeling well lately. She has lost interest in most things, seems to be somber most of the time, and over the past few days has not gotten out of bed. The player is asked whether they could help her. After the video, the adolescents were told that they would play the game for five days. Each morning, when they would start the game while still at home, they would wake up in Lisa’s house and would be able to do five things for her (eg, get her something to drink). Some of those actions would be positive, while others would be negative. After they would choose five actions, they would go to school and their day would start. During the day at set time points, they would get feedback from Lisa about what they did in the game through automated text messages. They would earn points for their actions; together these points would add up to a total *Relationship* score, which would be shown in the menu of the game. That score would illustrate the quality of their relationship to Lisa and at the same time gives the research team an indication of the adolescents’ first aid skills through the actions they took to help Lisa in a more targeted and constructive way. The adolescents were also told that they could share the messages with each other and that sharing them might give them more information about the game and more quickly improve their skills in the game. Lastly, they were told that if they had questions or wanted to discuss what they had seen in the game before the contact session at the end of the intervention, they could go to their school welfare coordinator or school counselor.

The video game has a menu (see Figure 3) with buttons to access the house and Lisa’s messages, as well as a meter for the *Relationship* score. The menu also shows which of the five playing days the player is on and includes a button that leads players to an information page within the game. The information page shows the player’s personal ID and has a button they can press when they “feel like giving up on life.” If the player presses the button they are immediately directed to the 113 Zelfmoordpreventie (Suicide Prevention) website, the Dutch organization for suicide prevention, where they can chat or have a call with a trained volunteer. The 113 Zelfmoordpreventie website helps both adults and youth.

Within the house (see Figure 4), players are able to walk around, examine objects, talk to Lisa, and perform actions. Through interactions with Lisa, we aimed to increase the players’ ability to recognize depressive symptoms. There is no limit to walking, examining, or talking; however, players are only able to perform five actions per day, which are all related to good or bad first aid skills [27] and which will increase or decrease the Relationship score with Lisa. Once players perform those five actions, they are asked whether they wanted to go to school or redo the day. Playtime of the game per day is approximately 10-15 minutes. During the day, the entire class receives personal messages at the same time from Lisa, with feedback on their personal actions through text messages. Through the feedback, we aimed to increase players’ knowledge of help-seeking options and improve their first aid skills. The feedback moments are mainly scheduled during break times, so the players will have the opportunity to discuss the messages and talk about game strategies.

**Figure 1 figure1:**
[figure not shown]
Flowchart of the study design.

**Figure 2 figure2:**
[figure not shown]
Moving Stories' video game character, Lisa (screenshot; translated to English).

**Figure 3 figure3:**
[figure not shown]
Moving Stories menu (screenshot, translated to English).

The goal of the game is for players to build a relationship with Lisa by showing interest, trying to help her feel a little better, and following up on promises. The end goal of the game is to get an adult involved, after discussing this with Lisa. When the player reaches a *Relationship* score of 50, Lisa gets out of bed. When the player reaches a *Relationship* score of 95, Lisa will be willing to talk to an adult about what is going on. Only when the player discussed this with her, and she mentioned she was willing, does the action of calling an adult get rated positively. After five days of playing, all players see a final scene that takes place a few months into the future. In the scene, Lisa tells the player that she got help and that she is getting better. Based on the final *Relationship* score, Lisa thanks the player for their efforts during the time they were in the house and gives specific feedback on what the player could have done to further help her.

**Figure 4 figure4:**
[figure not shown]
Lisa's house in Moving Stories (screenshot).

After five days of playing, the program finished with a contact session. In this concluding session, the story of the girl in the game was brought into the real world. A trainer with lived experience with depression led the contact session. All trainers have been trained by the Trimbos Institute in telling their story, guiding a discussion about the game, and translating their story and that of the game to specific first aid skills. In the session, the trainer told their own story and used the experiences of the adolescents in the game to discuss five first aid skills the adolescents could go back to when they want to help a friend who might be suffering from depression. These five skills, or action points, in helping a friend were based on content from the teen Mental Health First Aid training [24] and have been translated into Dutch: (1) Look for warning signs, (2) Ask how they are, (3) Listen without judgment—“without judgement” was added specifically to this program, (4) Help them connect with an adult, and (5) Be a friend. During the contact session, adolescents were allowed to ask questions about the game and about the experience of the trainer. To guide the discussion, the trainer used a PowerPoint presentation with predetermined questions that were related to the content of the game and the five action points. A member of the research team was present to make sure that all questions were discussed.

Moving Stories has been developed through a close collaboration between game designers and behavioral scientists using an iterative design process (see Figure 5). This means that multiple prototypes have been tested in pilot studies before the final version was built. All stakeholder groups have been involved during each development phase, including youth, therapists, and teachers. The concept of the game was based on the latest literature and best practice experiences. In total, we ran through five iteration rounds, each with several playtests. Over 200 people played the game before final development.

### Procedure

Participants are adolescents in the second year of high school (ie, 12-15 years old). Schools in the Netherlands were approached and asked to participate with at least two second-year classes to allow for within-school randomization. The exclusion criterion was refusal from either the parent or the adolescent to participate.

After schools agreed to participate, the classes were allocated to either the Moving Stories or control condition by an independent researcher using computer-generated random numbers. All parents and adolescents in the participating classes received an information letter via the school with information about the study (see Multimedia Appendix 1). Along with the letter, parents received a consent form, which they had to sign and send back to the researchers in order to give consent for their child’s participation. Before adolescents filled in the pretest, they will also had to give written active consent for participation. All questionnaires at all assessment points were Web based and were either filled in at school or at home.

**Figure 5 figure5:**
[figure not shown]
Iterative design process for the development of Moving Stories. RCT: randomized controlled trial.

To verify that Moving Stories does not increase depressive symptoms or suicidal ideation in adolescents, the Child Depression Inventory (CDI) [37,38] was administered. At all assessment points, if adolescents had a score on depressive symptoms in the clinical range and/or suicidal intention (CDI>29 and/or a score of 2 on question 9 of the CDI) [37,38], both the parents and adolescent were contacted by phone by a clinically trained member of the research team to inform them of the result and to give advice on where to seek professional help. We follow standard Dutch guidelines, in which we refer adolescents and their parents to the appropriate professional channels of care, where they will receive an assessment and subsequent intake if necessary. No follow-up of this group will be initiated from the research team itself. This procedure was approved by the Research Ethics Committee and complies with Dutch care guidelines. Adolescents who were contacted were not excluded from participating in the study, since that would increase stigma. During analyses, we will check and, if necessary, control for the possible effects of contacting participants and referring them to care.

To make sure that all adolescents who seek help from teachers during the study receive the help that they need, all teachers were provided with an information booklet developed for this study that includes short practical tips on what they can do to help their students. The primary researcher informed the teachers and other professionals involved at the school about the study and the short practical tips at an information session. In addition, teachers had the opportunity to follow an e-learning program on suicidality and depression in youth. This program, called Mental Health Online [39], aims to improve knowledge and self-confidence in people working with youth and has been found to be effective [40]. For this study, the developers of Mental Health Online have added an information page on depression to the program, since the e-learning program mainly discusses suicidality in youth [41] (in Dutch).

At pretest, adolescents were provided with a participant number by the researcher to fill out the questionnaires. They also received a personal player ID in the game. The data from the questionnaire and the data from the game will be matched through the participant number and personal player ID. Adolescents filled in their names and contact information during the pretest; this information can only be accessed by the primary researchers ([name]) and data management team at the Trimbos Institute (Dutch National Institute on Mental Health and Addiction) for the purpose of calling adolescents and their parents in case of clinical depressive symptoms and/or suicidal ideation. Adolescents were reminded, through email or via a phone call, to fill in the questionnaires. Data are stored on a secure server in accordance with European privacy law.

We expected that most adolescents would have had a suitable mobile phone or tablet that can run the video game Moving Stories. If an adolescent did not have a mobile phone or tablet that was suitable for the video game, a mobile phone was provided by the research team for the duration of the program. Adolescents received €12.50 in total for filling in the questionnaires at the four assessment points. Both parents and adolescents were allowed to withdraw their consent at any time during the study without consequences. Ethical approval for this study was provided by the Ethical Committee of the Faculty of Social Sciences at the Radboud University Nijmegen (ECSW2017-2306-526). This study is registered in the Dutch Trial Register (NTR7033).

### Measures

#### Descriptives

Sociodemographic variables include gender, age, ethnicity, and current educational level. We measured prior gaming experience by asking participants if they play video games and, if so, on what platforms and how many hours per week they play video games.

#### Depressive Symptoms

The CDI [37,38] was used to control for depressive symptoms. The questionnaire consists of 27 items, each with three statements to choose from. Participants were asked to pick the statement that best described how they felt in the previous two weeks. An example of an item’s three statements is as follows: *I sometimes feel sad; I often feel sad; I always feel sad*. Each statement corresponds to a score of 0, 1, or 2. Scores are added up to a total score for depressive symptoms. The Dutch version of the CDI has good internal consistency and test-retest reliability [42].

#### Outcome Measures

##### Overview

Mental health literacy regarding depression was measured by (1) symptom recognition, (2) first aid intentions, (3) knowledge of first aid, (4) first aid confidence, (5) beliefs about help, and (6) help-seeking intentions. Depression stigma was measured by (1) personal stigma, (2) perceived stigma, and (3) social distance. For an overview of all measures used and the relative assessment points, see Multimedia Appendix 2. All measures that did not have a Dutch version have been translated into Dutch and translated back into English by an independent researcher. Incongruities were discussed and resolved. Cronbach alpha values will be calculated for all measures with more than one item.

##### Symptom Recognition

Symptom recognition was assessed by using three vignettes with gender-matched descriptions of 15-year-old adolescents with depression, social anxiety, and psychosis, respectively [43]. Participants were asked what might be going on with this person. Responses were open ended. The symptom *irritability* has been added to the depression vignette, since this is considered an important symptom in adolescence [44]. Correct scores in the depression vignette are defined by labeling the person as depressed or by using a word related to depression. Overestimation of depression is defined by labeling the person in the social anxiety and/or psychosis vignette as depressed or by using a word related to depression. For the following items, the vignette of the person with depression was used as an example.

##### First Aid Confidence

Confidence in providing first aid was measured by asking how confident the participant would be to help the person in the vignette if he or she was their friend: 5-point scale from 1 (not at all confident) to 5 (very confident) [24].

##### First Aid Intentions

To measure general first aid intentions, participants were asked how much they agree with the statement “If [name] was a friend, I would help him/her”: 5-point scale from 1 (totally disagree) to 5 (totally agree). Specific first aid intentions were assessed by asking whether they would perform the mentioned first aid action “if [name] was a friend”: 5-point scale from 1 (never) to 5 (certainly). In total, six helpful (eg, “Tell [name] I have noticed something seems wrong and I want to make sure s/he is okay”) and six harmful (eg, “Ignore [name] because s/he is being attention-seeking”) actions were mentioned [28] and an open-ended option was provided (eg, “I would do something else other than the options mentioned above, namely...”). The scores for the harmful actions will be reverse scored. A total score for first aid intentions per scale will be calculated by summing up the scores for the helpful actions and the reverse-scored harmful actions, with higher scores representing better first aid intentions. Both scales have acceptable-to-good reliability [28].

##### Beliefs About Help

Beliefs about help were assessed by asking whether the following 10 people would make person’s situation in the vignette *better*, *not better*, *not worse,* or *worse*: (1) boyfriend or girlfriend; (2) friend (not related); (3) parent; (4) other relative; (5) psychologist or social worker (outside school); (6) phone helpline; (7) general practitioner; (8) teacher; (9) school welfare coordinator or school counselor; and (10) religious leader (eg, priest, imam, or rabbi). They were also asked who of those 10 would be most helpful. The number of selected adult sources deemed to be helpful (*better*) will be used to calculate beliefs about appropriate help: the *other relative* category will be excluded, since it could include an adult *or* peer [24].

##### Stigma

Both personal and perceived stigma was measured using the Dutch Depression Stigma Scale [45]. Any mention of the word *depression* was substituted by the situation of the person in the vignette (eg, “[name] is *dangerous*,” similar to the procedure in Jorm and Wright [46]). The last two statements in the scale about hiring a person with depression and voting for them if they were a politician were not used because we do not consider those relevant for this age group. The original personal and perceived stigma scales both have acceptable-to-good internal consistency [47]. Social distance was measured with the five items from the Social Distance Scale for youth [46]. The Social Distance Scale for youth has excellent internal consistency [28].

##### First Aid Behavior

First aid behavior was measured by asking whether the participant has had contact with someone who has experienced a problem similar to that seen in the vignette within the last three months. A problem is defined as when “someone has changed a lot in his/her normal thoughts, feelings, and behavior, which made it hard for him/her to move on with his/her life. The situation did not resolve itself and went on longer than you had expected.” If the participant answered *yes* or *maybe*, they were then asked whether they offered the other person their help. If so, or if they are unsure, they were asked what they did out of the 12 actions and the open-ended option mentioned in the First Aid Intentions section above. First aid behavior will be calculated similar to that of first aid intentions [28].

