### Objectives

The goal of this paper is to describe the protocol for a study that will test the effectiveness of the program Moving Stories in a Dutch adolescent sample by means of a randomized controlled trial. Our first hypothesis is that adolescents who participate in the Moving Stories program will have better mental health literacy and will endorse fewer stigmatizing attitudes regarding depression than adolescents who do not participate, both directly at posttest and at 3- and 6-months follow-up. Second, we expect a change in help-seeking and first aid behavior. At 3- and 6-months follow-up, we expect that adolescents in the Moving Stories group, compared to the control group, will have sought more help if they were experiencing depressive symptoms or provided increased appropriate first aid if they were in contact with a peer who was experiencing depressive symptoms.

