##### Help-Seeking Behavior

Help-seeking behavior was assessed by asking whether the participants themselves had experienced a problem similar to the situation in the vignette. If they responded with *yes* or *not sure*, they were asked whether someone has helped them with this problem in the last three months and who this person was: multiple options were allowed. We did not distinguish between whether the help was provided to the participant or whether they sought out the help from this person themselves. The same list of people from the Beliefs About Help section and the GHSQ [24,48] was used with the additional response option *Don’t know for sure*. If the participant indicated their boyfriend or girlfriend and/or a friend had helped them, they were asked what that person did out of the 12 first aid actions and the open-ended option mentioned in the First Aid Intentions section above [28]. This was done in order to assess the first aid skills in youth surrounding the person who had experienced a problem such as that in the vignette.

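### The first-aid behavior score exists only for pupils who report a contact and then helped or are unsure, so comparing it between arms is not protected by randomization

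*Protocol article*

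**What the plan says.** All references are to the Protocol article.

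- **Objectives.** The first-aid part of Hypothesis 2 is that, at 3 and 6 months, the program group will have "provided increased appropriate first aid if they were in contact with a peer who was experiencing depressive symptoms". The condition is contact, not having helped.
- **First Aid Behavior.** The item is routed. Pupils first report whether, in the last three months, they had contact with someone with a problem like the one in the vignette. After a yes or maybe, "they were then asked whether they offered the other person their help". Then: "If so, or if they are unsure, they were asked what they did out of the 12 actions".
- **Scoring.** "First aid behavior will be calculated similar to that of first aid intentions". Under First Aid Intentions that means summing the helpful actions and the reverse-scored harmful ones. No value is given for a pupil who leaves the routing before the actions.
- **Help-Seeking Behavior.** This starts by "asking whether the participants themselves had experienced a problem similar to the situation in the vignette", and only a yes or not sure leads on to questions about who helped. No score is defined.
- **Program.** The first listed target is "recognition of when a disorder is developing"; first aid skills are another.
- **Design.** Behavior is not assessed at posttest, so the relevant answers come at the two follow-ups.
- **Statistical Analyses.** All children with a pretest enter the tests of the hypotheses. Regression is named for literacy and stigma; no model is named for behavior.

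**The concern.** Randomization makes whole arms comparable. It does not make comparable the pupils in each arm who later pass a filter, if the program changes who passes. Here the two filters are noticing a problem in someone else and offering help. The program teaches recognition, which bears on the first, and helping, which is the second.

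The second filter is the more serious. Offering no help to a peer in difficulty is exactly the failure that Hypothesis 2 is about, and the score leaves those pupils out. If the program moved hesitant pupils from doing nothing to giving modest help, the intervention mean could fall because those pupils now have a score, although more pupils helped.

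Behavior is one of the trial's two hypotheses, and the Introduction and Discussion present it as what sets this program apart from earlier ones.

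**Working it through.** **1. The plan's own figure.** The total of 180 reproduces.

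- Design effect: 1 + ((0.19² + 1) × 18 − 1) × 0.02 = 1.353.
- Unadjusted n per arm: 2 × (1.960 + 0.842)² / 0.40² = 98.1.
- Baseline adjustment with two follow-ups and all correlations 0.50 gives a variance factor of (1 + 0.5)/2 − 0.25 = 0.50. Then 98.1 × 0.50 = 49.06, so 50 per arm.
- 50 × 1.35 / 18 = 3.75 classes, rounded to 4, plus 1 = 5; and 5 × 18 × 2 = 180.

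This was sized for literacy and stigma in all 90 pupils per arm. It neither supports nor contradicts the point about behavior.

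**2. The texts side by side.**

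| Pupil at follow-up | Within Hypothesis 2 (first aid)? | Promised in the analysis? | Has a 12-action score? |
|---|---|---|---|
| Reports no contact | no | yes | no |
| Reports contact, offered no help | yes | yes | no |
| Reports contact, helped or unsure | yes | yes | yes |

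The second row is the inconsistency. It follows from the stated scoring rule, whatever model is used later.

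**3. How far the filters could mislead.** The article gives no pass rates, so every rate below is an assumption.

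*Worked example, 90 per arm.* Each arm has 12 severe and 24 mild contacts. Helping is 75% for severe and 40% for mild in both arms. Controls report all severe and 8 mild contacts; the intervention arm reports all severe and 16 mild.

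- Control: helped = 12 × 0.75 + 8 × 0.40 = 12.2. Among reported contacts 12.2/20 = 61%; among all pupils 12.2/90 = 13.6%.
- Intervention: helped = 12 × 0.75 + 16 × 0.40 = 15.4. Among reported contacts 15.4/28 = 55%; among all pupils 15.4/90 = 17.1%.
- Reported contacts left without an action score: 20 − 12.2 = 7.8 in controls and 28 − 15.4 = 12.6 in the intervention arm.

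The conditional rate suggests harm and the all-pupil rate suggests benefit. The example concerns the proportion helping, not the action score.

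*Selection model for the score.* Let first-aid quality and the tendency to pass the filters be bivariate normal with correlation ρ, with no program effect on quality. The mean among those passing is ρ·φ(c)/p, with c = Φ⁻¹(1 − p). The bias is the intervention value minus the control value. Type I error is two-sided, nominal 5%, and ignores clustering.

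| Pass rate, control → intervention | ρ = 0.3: bias (SD), type I error | ρ = 0.5: bias (SD), type I error |
|---|---|---|
| 20% → 20% | 0, 5.0% | 0, 5.0% |
| 20% → 30% | −0.07, 5.7% | −0.12, 7.2% |
| 20% → 40% | −0.13, 7.5% | −0.22, 13.3% |
| 30% → 40% | −0.06, 5.6% | −0.10, 7.0% |
| 30% → 50% | −0.11, 7.5% | −0.18, 12.9% |

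Equal pass rates give no bias in this model. A negative ρ would reverse the sign.

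**4. Subset size.** If 50%, 30% or 20% of 90 pass, then 45, 27 or 18 pupils per arm carry a score. With the design effect recomputed for the smaller classes, power for d = 0.40 is 70%, 51% or 38% at the plan's variance factor of 0.50, and 53%, 37% or 27% with one follow-up (factor 0.75).

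**5. Limit of the all-pupil outcome.** In the worked example, suppose the unreported mild contacts were also helped at 40%. True helping is then (12 × 0.75 + 24 × 0.40)/90 = 18.6/90 = 20.7% in both arms. The reported rise from 13.6% to 17.1% would be labelling only.

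**The case against.** The strongest reply is that the article describes questionnaire routing and names no model for Hypothesis 2, so how unscored pupils enter may be settled in an analysis plan that is not shown. That holds for the model. It does not hold for the score, whose rule is stated and gives non-helpers no value.

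Second, conditioning on contact is the stated question, and whether help was offered is recorded for everyone reporting contact. Both are correct. Pupils who did nothing are therefore identifiable in the data; it is the action score that loses them. This is why the repair needs only rescoring.

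Third, the problem definition asks for a visible, lasting change rather than a diagnosis, and maybe answers pass. This weakens the link between recognition and the contact filter but does not remove it, because the judgement remains the pupil's. It does not touch the offered-help filter.

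Some stronger readings are tempting but unsupported:

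- *That help-seeking is mis-scored in the same way.* It has a similar self-reported filter, but no score or model is defined for it. Only a caution against restricting the comparison to pupils reporting a problem is warranted.
- *That unasked items will be imputed.* Statistical Analyses mentions software features for missing data, not their use on items skipped by routing.
- *That the trainer with lived experience would count as a contact.* With a three-month recall, the session lies outside the window at 6 months and at its edge at 3 months.
- *That the result will be biased against the program.* The article contains nothing that fixes a size or a direction.

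**Conclusion.** The concern holds for the first-aid action score. As defined, it exists only after two post-randomization filters that the program aims to shift. It omits pupils whom Hypothesis 2 includes and whom the analysis section promises to include, so a between-arm comparison of it is not a protected randomized comparison. The limitations in the Discussion cover self-report and the lack of objective behavioral measures, but not this selection.

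The size is unknown. Under the assumed pass rates and correlations the spurious difference runs from 0 (equal rates) to about 0.22 SD, set against the d = 0.40 that the trial was planned to detect for literacy and stigma. The conclusion rests on the program changing either how many pupils pass or which pupils pass; if it changes neither, there is no bias.

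This should be fixed before behavior is analysed by arm. It does not affect the literacy and stigma analyses or the sample size.

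**What to change.** - **First aid.** Test this part of Hypothesis 2 in all pupils by randomized arm, as reported contact and gave appropriate help (yes/no). Score no contact or no help as no. Define in advance what counts as appropriate from the 12 actions, and how unsure answers are scored.
- **Help received.** Handle it the same way, yes/no in all pupils. Add a secondary analysis in pupils with elevated CDI at T1, with the cut-off stated in advance; that subgroup is fixed before the program starts.
- **Filters.** Report by arm the proportions reporting contact, reporting an own problem and offering help, the last also among those reporting contact.
- **Action score.** Present the 12-action score among helpers as descriptive only.
- **Skipped items.** State that items skipped by routing are not missing data; a questionnaire not returned is.

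The cost is rescoring of collected data and some wording in the analysis plan. Two drawbacks should be stated with the results. Pupils who had no occasion to act dilute the effect. The all-pupil outcome also still depends on self-reported contact, so a rise may partly reflect more labelling of contacts rather than more helping. The filter proportions let the reader judge this.
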